The primary aim of the present study is to assess whether adding lithium to standard therapy is an effective treatment strategy to reduce the risk of suicidal behaviour in long term treatment of people with TRD and previous history of DSH. Secondary aims of the study are: (a) to assess whether adding lithium has a specific impact in improving depressive symptoms; (b) to assess the long term tolerability profile of the lithium-augmentation strategy.

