## Methods/Design

In a multi-centre, 12-month, superiority trial, we will randomise patients with TRD and history of DSH to (i) add lithium to usual treatment (add-on lithium strategy) or (ii) avoid lithium in usual treatment (without-lithium strategy). To be as close as possible to clinical practice, patients and clinicians will not be blind to treatments provided during the trial. However, to limit the potential bias introduced by lack of blindness, an independent adjudicating committee, blind to treatment allocation, will validate the events that will constitute the primary outcome. Patients will be assessed at baseline before randomisation and then every month after random allocation until the completion of the 12-month follow-up. All phases of the trial will be recorded following the CONSORT statement [17,18].

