#### Exclusion criteria

(a) A primary diagnosis of any concurrent Axis I disorder (according to DSM-IV criteria) other than major depression (by contrast, any concurrent DSM-IV Axis II disorder will not constitute an exclusion criterion).

(b) Previous exposure to lithium associated with lack of efficacy or adverse reactions.

(c) Clinical conditions contraindicating lithium (i.e., thyroid or kidney disease/abnormalities).

(d) Pregnant/lactating women and women of childbearing potential not practicing a reliable method of contraception.

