### Baseline and follow up assessments

Before entering the study, patients will be asked to provide informed consent to participate. The following information will be collected at baseline: sociodemographic and clinical characteristics, diagnosis according to the Mini Neuropsychiatry Interview (MINI) [19], laboratory and electrocardiography (ECG) parameters, severity of illness according to the Quick Inventory Depression Scale (QIDS) [20], a self-rated instruments that has been shown to have good psychometric properties [21]. Detailed information will be gathered on previous DSH acts, as well.

Follow-up data will be obtained each month after random allocation using an electronic form, as follows: any death or DSH, lithium oral dose and plasma level (if applicable), concomitant drug treatments, QIDS scores, adverse events and information on laboratory and ECG parameters.

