### Outcomes

Suicide completion and acts of DSH during the 12 months of follow-up will constitute the composite primary outcome. The term “suicide” is defined as an act with a fatal outcome, deliberately initiated and performed by the person with the knowledge or expectation of its fatal outcome. DSH is defined as intentional self-poisoning or self-injury, irrespective of motivation, as the intention to end life may be absent or present to a variable degree [7,8]. To preserve outcome assessor blindness, an independent adjudicating committee (three clinical psychiatrists, with no links to the study and blind to treatment allocation) will anonymously review all deaths and all hazardous acts reported during the 12 months of follow-up by the treating clinicians. The committee will have the role of identifying, among deaths, the cases of suicide, and among hazardous acts those that constitute acts of DSH. Only the cases of suicide and those of DSH validated by the committee will constitute the primary outcome.

As secondary outcomes, we will consider number of events (acts of DSH), number of suicides and all-cause mortality, change in severity of depressive symptoms from baseline to endpoint and adverse reactions during the 12 months of follow-up.

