Time from randomised treatment assignment until all-cause mortality during the 12 months of follow-up will be analysed through a log-rank test for difference in survival between the two groups. The same method will be applied for the following secondary outcomes: suicide mortality, deliberate self-harm. Multivariate analyses will be performed to explore the possible role of prognostic factors on outcomes.

Change in severity of depressive symptoms from baseline to 12 months will be analysed as a continuous variable and as a dichotomous variables, where individuals showing an improvement of al least 50% will be considered treatment responders. Change in severity of illness at 12-months will be compared between the two groups of treatment through appropriate statistical methods for repeated measurements (paired t-test or McNemar non parametric test according to the variables distribution). The number of events/outcomes of interest (suicide or DSH) will be compared between the two groups of treatment through the chi-square test (or the Fisher’s exact test when appropriate). When possible, a multivariate analysis will be performed through a Poisson regression model with a robust error variance.

The proportion of patients with adverse reactions during the study will be compared between the two groups of treatment through the chi-square test (or the Fisher’s exact test when appropriate).

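### Adverse events are collected, but the tolerability test is worded for adverse reactions; read as written, it would rest on a label assigned without blinding

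*Protocol article*

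**What the plan says.** The Background section of the Protocol article gives as its second secondary aim "to assess the long term tolerability profile of the lithium-augmentation strategy".

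Three places deal with the data for that aim:

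- **Collection.** Under Baseline and follow up assessments, the monthly form for all randomised patients includes "concomitant drug treatments, QIDS scores, adverse events and information on laboratory and ECG parameters".
- **Outcome.** Under Outcomes, the secondary outcomes end with "adverse reactions during the 12 months of follow-up".
- **Test.** Under Statistical analysis: "The proportion of patients with adverse reactions during the study will be compared between the two groups of treatment", by chi-square or Fisher's exact test. No other comparison of adverse events or reactions is described.

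On blinding, Methods/Design states that "patients and clinicians will not be blind to treatments provided during the trial". The independent blinded committee described under Outcomes "will anonymously review all deaths and all hazardous acts reported during the 12 months of follow-up by the treating clinicians". Its task is to identify suicides and acts of deliberate self-harm; adverse events are not part of it.

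**The concern.** The variable collected and the variable tested have different names, and the article gives no rule that leads from one to the other. In ordinary use an adverse event is anything untoward that happens, while an adverse reaction is an event put down to a drug. If the outcome is built on the second meaning, someone has to make a causal judgement for each event. Here the people in a position to make it know the allocation, and one arm has lithium added by design while the other may not receive it and has no placebo described in its place.

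The difference between arms would then combine two things: how often events occur, and how readily they are blamed on a drug. Readier attribution in the lithium arm could produce an apparent harm. Less ready attribution there, for example because symptoms are put down to the depression, could conceal a real one. The masking of the trial biostatistician does not help, because the label would already be fixed when the data arrive.

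**Working it through.** **1. The wording, side by side.** The plan gives no figure on this point, so there is nothing to reproduce and the check starts with the text.

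| Place in the Protocol article | Term | Role |
|---|---|---|
| Baseline and follow up assessments | adverse events | collected monthly, both arms |
| Outcomes | adverse reactions | secondary outcome |
| Statistical analysis | adverse reactions | between-arm test |
| Exclusion criteria, item (b) | adverse reactions | past reactions to lithium |

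The outcome and the test agree with each other and differ from the data collected, so this is not a single slip. The only other use of the term, "Previous exposure to lithium associated with lack of efficacy or adverse reactions", ties it to a drug, which fits the ordinary meaning. The article does not define the term.

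**2. How attribution enters the test.** Let e be the proportion of patients in an arm with any adverse event, and a the share of those patients who are labelled as having a reaction. The test compares e × a between arms, and the ratio of the two arms is

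(e_L / e_C) × (a_L / a_C).

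If a_L = a_C, the ratio of true event proportions is preserved. If a_L > a_C, a difference can appear although e_L = e_C. If a_L / a_C = e_C / e_L, a true difference cancels completely.

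**3. Illustration on assumed rates.** The 105 patients per arm come from Power analysis and sample size calculation. Everything else here is assumed: 42/105 (40%) with any event in each arm, so no true difference.

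- 70% v 30% attribution: 42 × 0.70 = 29.4, taken as 29; 42 × 0.30 = 12.6, taken as 13.
- 60% v 40% attribution: 42 × 0.60 = 25.2, taken as 25; 42 × 0.40 = 16.8, taken as 17.

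In both cases the pooled proportion is 42/210 = 0.20, so the standard error of the difference is √(0.20 × 0.80 × 2/105) = 0.0552.

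- 29 v 13: difference 16/105 = 0.1524, z = 0.1524/0.0552 = 2.76, p = 0.006 (chi-square without continuity correction; Fisher p = 0.009).
- 25 v 17: difference 8/105 = 0.0762, z = 0.0762/0.0552 = 1.38, p about 0.17.

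**4. Range over assumptions.** With 105 per arm, equal all-cause proportions and two-sided α = 0.05, let p₁ and p₂ be the labelled proportions and p̄ their mean. The approximate chance of a significant difference is

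Φ{ (|p₁ − p₂| − 1.96 √[2p̄(1 − p̄)/105]) / √[(p₁(1 − p₁) + p₂(1 − p₂))/105] }.

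For example, a 50% all-cause proportion with 60% v 40% attribution gives p₁ = 0.30 and p₂ = 0.20, hence Φ{(0.10 − 1.96 × 0.0598)/0.0594} = Φ(−0.29) = 0.39.

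| Attribution, lithium v control | All-cause 30% | All-cause 50% | All-cause 70% |
|---|---|---|---|
| equal | 5% | 5% | 5% |
| 50% v 40% | 9% | 14% | 19% |
| 60% v 40% | 23% | 39% | 57% |
| 70% v 30% | 69% | 92% | 99% |

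The equal row is the nominal level of the test. The result depends almost entirely on how far attribution differs between arms, and the documents give no information on that.

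**The case against.** The strongest reply is that the two terms may simply be used as synonyms. The monthly form is the only described source for this outcome, and it lists adverse events with no causality field. The article is also a condensed account: a definition of adverse reaction, and a rule for who classifies it, commonly sit in the full protocol or analysis plan, so their absence here is no fault. Both points stand. What remains is what the article does state: it names the outcome and the test, and names them differently from the data.

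A reader might infer more than the text supports:

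- *That only events judged by clinicians to be drug-caused are compared.* The article never describes a causality assessment, says who would make one, or says that unrelated events are left out. This is an inference from the ordinary meaning of the word.
- *That only the lithium arm has a new drug to blame.* Under Interventions, both arms receive usual treatment and may be given any other drug; lithium alone is barred from the control arm. Unequal attribution is plausible, but not for so absolute a reason.
- *That the outcome must differ between arms even when events do not.* This needs both the attribution reading and unequal attribution. The milder assumed splits often give no significant difference.
- *That a comparison of all events would be unbiased.* The same unblinded patients and clinicians report the events.

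It is also fair to say that one harm comparison free of attribution, all-cause mortality, is already planned.

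**Conclusion.** The point holds in conditional form. The terms for collection and analysis do not match, and if the wording of the outcome and the test is followed in its ordinary sense, the tolerability result would depend on a label assigned without blinding and without independent review. That could create or hide a difference on a stated secondary aim.

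The size is unknown. The p-values of 0.006 and about 0.17, and the 9% to 99% chances of a spurious significant result under unequal attribution, rest wholly on assumed event and attribution rates. They show that the mechanism can matter at 105 per arm, not that it will. The primary outcome, its analysis and the sample size are untouched. The change is still worth making, because it is right on either reading: if the terms are synonyms it corrects the wording, and if they are not it removes the dependence on attribution.

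**What to change.** In the Outcomes and Statistical analysis sections, define the tolerability outcome as the proportion of patients with any adverse event recorded on the monthly form during the 12 months. Compare it by allocated arm regardless of attribution, with the chi-square or Fisher test already planned. If attribution to a drug is recorded, report attributed reactions descriptively, without a between-arm test.

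The cost is a change of wording, since adverse events are already collected each month in both arms. There are two drawbacks. Events unrelated to treatment add noise and may dilute a true difference. Reporting stays unblinded, so bias is reduced but not removed, and the trial report should say so. A separate comparison of serious adverse events would not be a wording change on the evidence of this article, because seriousness is not among the items listed as recorded.

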#### Data management

All study data will be entered in a computerised database and stored by the World Health Organisation Collaborative Centre for Research and Training in Mental Health and Service Evaluation of the University of Verona. The correctness and consistency of the data will be ensured by the double-entry technique and by a set of electronic and manual edit checks. In accordance with the Declaration of Helsinki, patients’ confidentiality will be preserved at all times and the contents of the recruitment and follow-up forms will not be disclosed to any third party. The data collected in the study corresponding to a patient will be recorded anonymously.

### Ethical aspects

This study will be conducted according to globally accepted standards of good clinical practice (as defined in the ICH E6 Guideline for Good Clinical Practice, 1 May 1996), in agreement with the Declaration of Helsinki and in keeping with local regulations. Study investigators will ensure that all persons assisting with the trial are adequately qualified, informed about the protocol, any amendments to the protocol, the study treatments, and their trial-related duties and functions. The coordinating centre will maintain a list of sub-investigators and other appropriately qualified persons involved in the study. Before being enrolled in the study, subjects will consent to participate after the nature, scope, and possible consequences of the clinical trial have been explained in a form understandable to them. An informed consent document that includes both information about the study and the consent form will be given to participants. This document will contain all the elements required by the ICH E6 Guideline for Good Clinical Practice and any additional elements required by local regulations. The document will be in a language understandable to the participants and will specify who informed the subject. The person who informs the subject will be a physician. After reading the informed consent document, the subject, or his/her legal representative, must give consent in writing. The subject’s consent must be confirmed at the time of consent by the personally dated signature of the subject and by the personally dated signature of the person conducting the informed consent discussion.

### Ethical approval document

The study has been approved by the Ethics Committee in Verona (coordinating centre) on May 6^th^ 2009 (EUDRACT number 2009-011409-17.

According to the ICH E6 Guideline for Good Clinical Practice, subjects who will be enrolled in the trial with the consent of the subjects’ legally acceptable representative will be informed about the trial to the extent compatible with the subjects’ understanding and, if capable, the subject will be asked to sign and personally date the written informed consent.

## Discussion

The results of this study should indicate whether lithium treatment is associated with lower risk of completed suicide and DSH in adult patients with treatment resistant unipolar depression, who recently attempted suicide. At present, evidence is lacking to indicate the most effective forms of pharmacological treatment for depressed patients with recent history of DSH. To answer this question is an important clinical issue, given the size of the DSH population and the risks of subsequent self-harm, including suicide. To our knowledge, this is the first study that will prospectively identify suicidal behaviour as an outcome measure and systematically assess it in a randomised design, recruiting a well-characterised and homogeneous sample of patients with treatment resistant major depression, with a high risk for suicidal behaviour. Moreover, as most meta-analyses of randomised clinical trials have not detected a reduction in number of suicides or suicide attempts in studies of antidepressants or anticonvulsants for mood disorders [24], the prospect of an agent with suicide-preventive properties is bound to have an enormous impact on the development of treatment strategies and clinical guidelines [25].

Designing our study, we aimed at being as close as possible to the real-world clinical setting. The recruiting centres will all be community based psychiatric services, where patients are not selected by diagnosis and are a representative subgroup of the general population. Even though this may enhance the external validity of the study and the generalisability of its findings, the heterogeneity of patient population might be an issue. High rate of DSH is usually found in patients with personality disorders (most of all, borderline disorder). This has clinical implications because patients with Axis II disorder comorbidity are clinically different from patients with major depression alone and borderline personality disorder can confer additional risk for suicidal ideation and DSH [26]. For this reason we stratified the randomisation, in order to have an equal distribution of treatment regimens in the two subgroups.

We are aware that to have standard care as comparison intervention may cause additional heterogeneity, as standard care may probably vary from centre to centre. Variability in standard aftercare of DSH patients in different regions (even though belonging to the same country, that is, Italy) may influence the relative effectiveness of experimental interventions in particular settings. In the final publication we will report all details of the standard care, as it is provided by clinicians who will prospectively collect precise data about the nature of the treatments patients will receive.
